#### 6.5. Safety assessment

Safety monitoring will be conducted throughout the study; therefore, safety concerns will be identified by continuous review of the data by the PI, clinic staff, clinical monitor, safety monitor, DSMB, and sponsor.

## **Specification of Safety Endpoints**

Safety will be assessed by evaluating reactogenicity (local reactions and systemic reactions such as fever, headache, and fatigue) during specified periods of the study. The following endpoints will be evaluated:

The nature, frequency, and severity of solicited AEs occurring from the time of injection through 14 days following the procedure (memory aid to assist)

The nature, frequency, and severity of unsolicited AEs from the time of injection through 28 days following the each injection

The nature, frequency, and severity of SAEs from the time of injection through the final study visit for each subject

## **Solicited Adverse Events**

A solicited AE is a predetermined event, which may reflect safety concerns related to the investigational product. The solicited AEs for this study include:

- Swelling, or pain at site of injection
- Fever
- Chills
- Myalgia (described to the subject as generalized muscle aches)
- Arthralgia (described to the subject as generalized joint aches)
- Swelling of joint(s) or pain on motion of joint(s)
- Rash or blisters of the skin
- Blisters or ulcers in mouth, tongue or gums
- Fatigue
- Headache
- Gastrointestinal symptoms (nausea, vomiting, abdominal pain, and/or diarrhea)

Participants with objective signs of arthritis (swelling, tenderness, warmth etc) will be evaluated with ultrasound.

Vesicular lesions and joint effusions (if tapped) will be sampled for PCR and virus isolation.

### **Serious Adverse Event or Serious Suspected Adverse Reaction**

An AE or suspected adverse reaction is considered “serious” if, in the view of either the investigator or sponsor, it results in any of the following outcomes:

- Death
- Life-threatening adverse event defined as any adverse drug experience that, in the opinion of the investigator, places the subject at immediate risk of death from the reaction as it occurred. It does not include a reaction that, had it occurred in a more severe form, might have caused death.
- Inpatient hospitalization or prolongation of existing hospitalization
- Persistent or significant disability/incapacity defined as a “substantial disruption of the ability to conduct normal life functions”
- Congenital anomaly/birth defect (in the offspring of a subject)

An AE or suspected adverse reaction is considered “life-threatening” if, in the view of either the investigator or sponsor, its occurrence places the patient or subject at immediate risk of death. It does not include an adverse event or suspected adverse reaction that, had it occurred in a more severe form, might have caused death.

Important medical events that may not result in death, be life-threatening, or require hospitalization may be considered serious when, based upon appropriate medical judgment, they may jeopardize the patient or subject and may require medical or surgical intervention to prevent one of the outcomes listed in this definition. Examples of such medical events include allergic bronchospasm requiring intensive treatment in an emergency room or at home, blood dyscrasias or convulsions that do not result in inpatient hospitalization, or the development of drug dependency or drug abuse.

### **Unexpected Adverse Event or Unexpected Suspected Adverse Reaction**

An AE or suspected adverse reaction is considered “unexpected” if it is not listed in the investigator brochure or is not listed at the specificity or severity that has been observed; or, if an investigator brochure is not required or available, is not consistent with the risk information described in the general investigational plan or elsewhere in the current application, as amended. For example, under this definition, hepatic necrosis would be unexpected (by virtue of greater severity) if the investigator’s brochure referred only to elevated hepatic enzymes or hepatitis. Similarly, cerebral thromboembolism and cerebral vasculitis would be unexpected (by virtue of greater specificity) if the investigator’s brochure listed only cerebral vascular accidents. “Unexpected,” as used in this definition, also refers to adverse events or suspected adverse reactions that are mentioned in the investigator brochure as occurring with a class of drugs or as anticipated from the pharmacological properties of the drug, but are not specifically mentioned as occurring with the particular drug under investigation.

## **Unanticipated Problems Involving Risks to Subjects Or Others**

Unanticipated problems involving risks to subjects or others must be reported to the IRB within 48 hours. These events encompass a broader category of events than SAEs and may include issues such as problems with loss of control of subject data or the investigational product; adverse psychological reactions; or breach of confidentiality. Risks to others (eg, program personnel) must also be reported.

Unanticipated problems involving risks to subjects or others are any incident, experience, or outcome that meets all of the following criteria:

- Unexpected (in terms of nature, severity, or frequency) given (a) the procedures that are described in the protocol, investigators brochure or informed consent document; and (b) the characteristics of the subject population;
- Related or possibly related to a subject's participation in the study; and
- Suggests that the study places subjects or others at a greater risk of harm than was previously known or recognized.

The DSMB will evaluate the PI's and research monitor's reports to determine whether a given incident, experience or outcome constitutes an unanticipated problem involving risk to subjects or others and, in coordination with the sponsor, ensure upward reporting of the unanticipated problems involving risk to subjects or others to the appropriate regulatory offices.

### **Relationship to Investigational Product**

The investigator must assign a relationship of each AE to the receipt of the investigational product. The investigator will use clinical judgment in conjunction with the assessment of a plausible biologic mechanism, a temporal relationship between the onset of the event in relation to receipt of the investigational product, and identification of possible alternate etiologies including underlying disease, concurrent illness or concomitant medications. The following guidelines should be used by investigators to assess the relationship of an AE to study product administration. Physicians will make this determination

- Not related: No relationship to investigational product. Applies to those events for which evidence exists that there is an alternate etiology.
- Unlikely: Likely unrelated to the investigational product. Likely to be related to factors other than investigational product, but cannot be ruled out with certainty.
- Possible: An association between the event and the administration of investigational product cannot be ruled out. There is a reasonable temporal association, but there may also be an alternative etiology such as the subject's clinical status or underlying factors including other therapy.

- Probable: There is a high degree of certainty that a relationship to the investigational product exists. There is a reasonable temporal association, and the event cannot be explained by known characteristics of the subject's clinical state or factors including other therapy.
- Definite: An association exists between the receipt of investigational product and the event. An association to other factors has been ruled out.

### Severity Assessment

All AEs will be assessed for severity by the investigator. Inherent in this assessment is the medical and clinical consideration of all information surrounding the event including any medical intervention required. Each event will be assigned one of the following categories: mild, moderate, severe, or life-threatening. Refer to the grading scale in annex 2 for further guidance in the assignment of severity. The criteria below may be used for any symptom not included in the grading scale. Any grade 4 (life-threatening) AE must be reported as an SAE.

The CRF for AEs will reflect only the highest severity for continuous days an event occurred.

- Mild      Grade 1      Does not interfere with routine activities  
Minimal level of discomfort
- Moderate      Grade 2      Interferes with routine activities  
Moderate level of discomfort
- Severe      Grade 3      Unable to perform routine activities  
Significant level of discomfort
- Potentially life-threatening      Grade 4      Hospitalization or ER visit for  
potentially  
life-threatening event

FDA guidelines for toxicity will be followed; however, if a subject is evaluated in an emergency room for nonlife threatening illness or symptoms (ie, visits emergency department on weekend for mild problems because the physician's office is closed), the information from that visit will be reviewed and severity of the adverse event will be assessed according to the subject's clinical signs and symptoms.

As defined by the ICH guideline for GCP, the term "severe" is often used to describe intensity (severity) of a specific event (as in mild, moderate, or severe myocardial infarction); the event itself however, may be of relatively minor medical significance (such as severe headache). This is not the same as "serious", which is based on subject/event outcome or action criteria usually associated with events that pose a threat to a subject's life or functioning. Seriousness (not severity) serves as a guide for defining regulatory reporting obligations.

### Recording Adverse Events

### Methods/Timing for Assessing, Recording, and Analyzing Safety Endpoints

Solicited AEs will be reviewed within the 14 days of vaccination utilizing the provided study memory aids. When a diagnosis is known, the AE term recorded on the CRF will be the diagnosis rather than a constellation of symptoms. The investigator will assess all AEs for seriousness, relationship to investigational product, severity, and other possible etiologies. When an event has not resolved by study closure, it will be documented on the AE CRF as “ongoing”.

The timeframe for the collection of unsolicited AEs begins at the first administration of investigational product through 28 days after the investigational product is administered. Solicited AEs will be collected from the time of administration of investigational product through 14 days following the procedure (assisted with a memory aid). The timeframe for the collection of SAEs begins at the first administration of investigational product through the end of the study.

All adverse events will be reported in concordance with ICH GCP reporting guidelines, with expedited reporting of SAEs being determined by these guidelines as well.

## 6.6. Immunogenicity Assessment

### Specification of Immunogenicity

#### Primary Immunogenicity Endpoint:

The primary immunogenicity endpoint is the ZEBOV-specific antibodies geometric mean titre via conventional ELISA. This information will allow calculation of seroconversion rates.

#### Secondary Immunogenicity Endpoint:

The secondary immunogenicity endpoint will be production of ZEBOV neutralizing antibodies after vaccination as measured by PsVNA. GMT as measured by PsVNA and PRNT50 titers on select samples will be determined for additional information.

#### Exploratory Endpoints:

There are multiple exploratory endpoints related to the immunological response to the vaccine. Endpoints include:

- Cross-neutralizing antibodies GMT using other Ebola PsV (eg, Sudan)
- Epitope studies with Ebola glycoprotein as target
- Human subjects will be genotyped based on HLA allele expression.
- Evaluation of the B cell repertoire before and after vaccination via Ig VDJ rearrangement sequencing and Ig heavy chain characterization
- Serum immunoglobulin characterization via mass spectrometry/proteomic analysis
- Characterization of epitope targeting for humoral response via domain programmable arrays
- Analysis of T cell repertoire via T cell receptor characterization
- Using multicolor flow cytometry, characterization of cellular response to vaccine antigen or peptides by intracellular cytokine staining (ICS) and the presence of surface markers that indicate cell lineage (CD4+, CD8+), activation status, and expression of selected activation markers.

- Isolation of Human Antibodies

The vaccine is eliciting a broad range of neutralizing antibodies. The genetic information of these antibodies can be isolated by the technology of phage display. For this, whole blood needs to be preserved in one Serum tube (2.5ml whole blood) and four PAXgene Blood RNA tubes (each tube à 2.5 ml whole blood). This blood withdrawal is needed 4 weeks after the last boost. From this blood whole RNA will be isolated, cDNA generated and the gene information from the variable fragments of the antibodies cloned into an appropriate phagemid system. From the resulting Fab-Phage Display Library, specific antibody fragments will be isolated, recombinantly produced and characterized for specific binding. The parallel blood withdrawal of serum is needed for preliminary tests of the blood samples for specific antigen reactivity.

|                                                          | Visit 1
Screening
Day -30/-1 | Visit 2
Vaccination
D0 | Visit 3
Follow-up
D1 | Visit 4
Follow-up
D2 | Visit 5
Follow-up
D7 | Visit 6
Follow-up
D14 | Visit 7
Follow-up
D28+/-7 | Visit 8
Follow-up
D56+/-7 | Visit 9
Follow-up
D84+/-7 | Visit 10
Follow-up
D180+/-14 |   |
|----------------------------------------------------------|------------------------------------|------------------------------|----------------------------|----------------------------|----------------------------|-----------------------------|---------------------------------|---------------------------------|---------------------------------|------------------------------------|---|
| Community engagement                                     | X                                  |                              |                            |                            |                            |                             | X                               |                                 |                                 | X                                  | X |
| Informed consent                                         | X                                  |                              |                            |                            |                            |                             |                                 |                                 |                                 |                                    |   |
| Full History                                             | X                                  |                              |                            |                            |                            |                             |                                 |                                 |                                 |                                    |   |
| Clinical examination                                     | X                                  |                              |                            |                            |                            |                             |                                 |                                 |                                 |                                    |   |
| Safety labs                                              | X                                  |                              |                            |                            | X                          |                             | X                               |                                 | X                               | X                                  |   |
| Additional Screening Labs                                | X                                  | X                            |                            |                            |                            |                             |                                 |                                 |                                 |                                    |   |
| medical history demo information                         | X                                  | X                            | X                          | X                          | X                          | X                           | X                               | X                               | X                               | X                                  |   |
| Inclusion/exclusion criteria                             | X                                  | X                            |                            |                            |                            |                             |                                 |                                 |                                 |                                    |   |
| pregnancy test counseling                                | X                                  | X                            |                            |                            |                            |                             |                                 |                                 |                                 |                                    |   |
| Randomization                                            |                                    | X                            |                            |                            |                            |                             |                                 |                                 |                                 |                                    |   |
| Review study visits and provide rulers, and thermometers |                                    | X                            |                            |                            |                            |                             |                                 |                                 |                                 |                                    |   |
| Provide emergency contact cards                          |                                    | X                            |                            |                            |                            |                             |                                 |                                 |                                 |                                    |   |
| Record concomitant medications                           | X                                  | X                            | X                          | X                          | X                          | X                           | X                               | X                               | X                               | X                                  |   |
| Physical Exam                                            | X                                  | X                            | X                          | X                          | X                          | X                           | X                               | X                               | X                               | X                                  |   |

|                                                             |     |   |     |     |     |     |     |     |     |     |  |
|-------------------------------------------------------------|-----|---|-----|-----|-----|-----|-----|-----|-----|-----|--|
| Monitor AEs                                                 |     | X | X   | X   | X   | X   | X   |     |     |     |  |
| Monitor SAEs                                                |     | X | X   | X   | X   | X   | X   | X   | X   | X   |  |
| Immunogenicity                                              |     |   |     |     |     |     |     |     |     |     |  |
| Serological analysis/repository                             | X   |   |     |     | X   | X   | X   | X   | X   | X   |  |
| T cell repertoire analysis                                  | X   |   |     |     | X   |     | X   |     | X   | X   |  |
| B cell repertoire analysis                                  | X   |   |     |     | X   |     | X   |     | X   | X   |  |
| Cellular repository                                         | X   |   |     |     | X   |     | X   |     | X   | X   |  |
| Viral isolation                                             | X   |   | X   | X   | X   |     |     |     |     |     |  |
| Antibody isolation                                          |     |   |     |     |     |     | X   |     |     |     |  |
| Blood Volume/visit (mL) adults                              | 140 |   | 6   | 6   | 75  | 60  | 108 | 20  | 80  | 92  |  |
| Cumulative volume for study adults                          | 140 |   | 146 | 152 | 227 | 287 | 395 | 415 | 495 | 587 |  |
| Blood Volume/visit (mL) children and adolescents            | 10  |   |     | 5   | 5   | 10  | 10  | 10  | 10  | 10  |  |
| Cumulative Blood Volume/visit (mL) children and adolescents | 10  |   |     | 15  | 20  | 30  | 40  | 50  | 60  | 70  |  |

**Table 3:** Study procedures.

## **7. Statistics**

Data analysis will consist of descriptive summaries for treatment groups. For primary endpoints, frequency on safety and reactogenicity events will be reported. For secondary and tertiary endpoints descriptive summaries and plots over the time course for both individual patient results and groups will be presented. Where appropriate highly skewed data will be log-transformed and presented as geometric means with 95% confidence intervals. Inference will be conducted with selected tests. For instance Fisher's exact test is used to compare seroconversion rate and percent of subject reporting AE between experimental groups. Logistic regression is used to evaluate the association between demographic information and seroconversion rate.

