| Stopping rules     | 
The study will be placed on safety hold in case of occurrence of a vaccine related SAE
                                                                                                                                                                                                                                                                                                                                                                                                                                                                                                                                                                                                                                                                                                                                                                                                                                                                                                                                                                                                                                                                                                                                                        |
| Sample Size        | 
– A total of 201 volunteers will be enrolled in this trial
 
 
• 20 Volunteers aged between 18 and 50 years inclusive, who will receive <math>3 \times 10^3</math> pfu of VSV<math>\Delta</math>G-ZEBOV vaccine IM
 
• 20 Volunteers aged between 18 and 50 years inclusive, who will receive <math>3 \times 10^4</math> pfu of VSV<math>\Delta</math>G-ZEBOV vaccine IM
 
• 20 Volunteers aged between 18 and 50 years inclusive, who will receive <math>3 \times 10^5</math> pfu of VSV<math>\Delta</math>G-ZEBOV vaccine IM
 
• 39 Volunteers aged between 18 and 50 years inclusive, who will receive <math>3 \times 10^6</math> pfu of VSV<math>\Delta</math>G-ZEBOV vaccine IM
 
• 62 Volunteer aged between 18 and 50 years inclusive, who will receive <math>2 \times 10^7</math> pfu of VSV<math>\Delta</math>G-ZEBOV vaccine IM
 
• 20 Volunteers aged between 13 and 17 years inclusive, who will receive <math>2 \times 10^7</math> pfu of VSV<math>\Delta</math>G-ZEBOV vaccine IM
 
• 20 Volunteers aged between 6 and 12 years inclusive, who will receive <math>2 \times 10^7</math> pfu of VSV<math>\Delta</math>G-ZEBOV vaccine IM.
 
 |

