| Statistical Methods | 
Every effort will be made to ensure that data collection will be harmonized between sites so that there is comparability and the ability to combine datasets as part of VEBCON network. Demographic variables and dose will be key associated variables. Fisher's exact test will be used to compare seroconversion rates and proportion of subjects who report AEs in each experimental group. Repeated measures analysis will be used to compare antibody titre between groups, with allowance for anticipated baseline seropositivity in some volunteers. A detailed statistical analysis plan will be developed during the course of this trial
                                                                                                                                                                                                                                                                                                                                                                                                                                                                     |
| Inclusion Criteria  | 
The volunteer must satisfy all the following criteria to be eligible for the study:
                                                                                                                                                                                                                                                                                                                                                                                                                                                                                                                                                                                                                                                                                                                                                                                                                                                                                                                                                                                                                                     |

- Healthy adult male or non-pregnant, non-lactating female, ages 18 to 50 (inclusive) at the time of screening, for cohorts 1-5
- Healthy male or non-pregnant female child or adolescent, ages 6-17 (inclusive) at the time of screening, for cohorts 6 and 7

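### The only method section 7 names for demographic associations is logistic regression on seroconversion, although the primary immunogenicity endpoint is the continuous ELISA titre; add a log-titre model

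*Protocol*

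**What the plan says.** Section 6.6 of the protocol sets the endpoint: "The primary immunogenicity endpoint is the ZEBOV-specific antibodies geometric mean titre via conventional ELISA". It then adds: "This information will allow calculation of seroconversion rates". Seroconversion is therefore a yes/no reduction of the titre, and no threshold is given for it.

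The Statistical Methods row of the synopsis says "Demographic variables and dose will be key associated variables". For titre it plans: "Repeated measures analysis will be used to compare antibody titre between groups, with allowance for anticipated baseline seropositivity in some volunteers".

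Section 7 is mainly descriptive, with log transformation and geometric means for skewed data. On inference it says: "Inference will be conducted with selected tests. For instance Fisher's exact test is used to compare seroconversion rate". For demographics it says: "Logistic regression is used to evaluate the association between demographic information and seroconversion rate". Section 7 does not mention the repeated-measures titre comparison or any allowance for baseline serostatus.

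The synopsis leaves detail to a later document: "A detailed statistical analysis plan will be developed during the course of this trial". On size it says: "A total of 201 volunteers will be enrolled in this trial".

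**The concern.** The synopsis gives demographic variables the same standing as dose, yet the one model named for them uses a cruder outcome than the endpoint that section 6.6 ranks first. The protocol gives no reason for the cut, such as a protective threshold.

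Two things follow. Differences in titre among people on the same side of the cut are discarded. And the nearer seroconversion comes to 100%, the fewer non-converters there are to carry the logistic model: at 95% among 102 people about five are expected (102 × 0.05 = 5.1), too few for several demographic terms. A real difference in titre by sex, or by age within adults, could then be missed or estimated unstably. An analyst who built the analysis from section 7 alone would carry forward only yes/no methods for comparing antibody response.

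**Working it through.** **No figure to reproduce.** The protocol states no power, effect size, titre SD, seroconversion rate, cut-off or test level for this analysis. Only the sample sizes come from the document (synopsis, Sample Size):
- All participants: 20 + 20 + 20 + 39 + 62 + 20 + 20 = 201.
- Those assigned 2×10^7 pfu: 62 + 20 + 20 = 102.
- Adults: 20 + 20 + 20 + 39 + 62 = 161.

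**Assumptions.** Log titre is normal with SD 1. A demographic factor splits the sample into two equal groups (51/51 or 100/101). The second group is lower by d SD. Seroconversion means a titre above a cut that gives rate p1 in the reference group. Tests are two-sided at 5%.

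**Titre analysis.** The two-sample t test has noncentrality d / √(1/n1 + 1/n2):
- N = 102, d = 0.2: 0.2 / 0.198 = 1.01, power 17.0%.
- N = 102, d = 0.4: 0.4 / 0.198 = 2.02, power 51.6%.
- N = 201, d = 0.4: 0.4 / 0.141 = 2.84, power 80.6%.

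**Seroconversion analysis.** The rate in the second group is p2 = Φ(Φ⁻¹(p1) − d). For d = 0.4 and p1 = 70 / 80 / 90 / 95%, p2 = 55.0 / 67.1 / 81.1 / 89.3%. Power of the two-group logistic likelihood-ratio test was found by summing the two binomial probabilities over all outcomes in which the statistic exceeds 3.84.

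| N | d | Titre | Logistic at p1 = 70 / 80 / 90 / 95% | Loss in points |
|---|---|---|---|---|
| 102 | 0.2 | 17.0% | 12.2 / 11.4 / 10.5 / 11.1% | 5 / 6 / 7 / 6 |
| 102 | 0.4 | 51.6% | 35.8 / 32.1 / 26.4 / 21.7% | 16 / 20 / 25 / 30 |
| 201 | 0.4 | 80.6% | 60.6 / 55.3 / 45.1 / 34.2% | 20 / 25 / 35 / 46 |

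Simulation of the same settings agrees to within about a point, giving for example 47 rather than 46 in the last cell.

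**Sensitivity.**
- *Direction.* If the second group is higher rather than lower, the loss at 0.4 SD grows to about 21 to 33 points (N = 102) and 27 to 55 points (N = 201).
- *Adults only.* With N = 161, d = 0.5 and overall seroconversion of 50 / 80 / 90 / 95%, simulated power is 87% to 89% for titre against 72 / 60 / 45 / 36% for the logistic model, a loss of about 16 to 53 points.
- *Wider range.* Over 0.2 to 0.8 SD, overall seroconversion of 50% to 95% and N = 161 or 201, the loss runs from about 0 to about 60 points. It is near zero where the effect is large and the cut is near the middle.
- *Test size.* With no true difference, N = 102 and 95% seroconversion, the likelihood-ratio test rejects 8.7% of the time rather than 5%, so its power there is flattered. The protocol does not say which test of the logistic coefficient would be used.

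**What these figures leave out.** They ignore dose, which spans 3×10^3 to 2×10^7 pfu across the 201. They also ignore baseline titre and use a simple post-vaccination cut, because the protocol defines none.

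**The case against.** Several parts of the other side's case stand.

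*Not exclusive.* A reader might infer that demographic effects are tested only on seroconversion. The text does not go so far: section 7 introduces its tests as selected examples, the synopsis does not tie demographics to seroconversion, and detail is left to an analysis plan not seen here. Nothing rules out a titre model with demographics. What remains is that the protocol itself names a method for this question, and it is the weaker one.

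*Age cohorts are covered.* A reader might take the synopsis' titre comparison to be between dose groups only. It says groups, and two of the seven groups listed in the synopsis are defined by age (13 to 17 and 6 to 12 years). The synopsis gives both the same 2×10^7 pfu as 62 adults. A comparison of adults, adolescents and children on the continuous titre is therefore already planned. The gap is sex, age within adults and other demographics.

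*No contradiction.* The repeated-measures analysis is missing from section 7, but the synopsis belongs to the same protocol and states it. This is a matter of tidiness.

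*No fixed power loss.* A reader might quote one range as the cost. With no effect size or seroconversion rate in the protocol, any range depends on its assumptions, and at 0.2 SD with 102 people the loss is small.

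*Limited consequence.* A reader might infer that dose choice by population is at risk. For age groups that does not follow: minors receive one dose level, so no titre model could choose among doses for them. The primary endpoints are safety, no objective or endpoint concerns demographic associations with titre, and the analysis is largely descriptive.

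*Seroconversion need not go.* It is a planned outcome with a planned Fisher comparison, and nothing here requires removing either.

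**Conclusion.** The point holds as a modest one. For demographic associations section 7 names only a model of dichotomised titre, while section 6.6 puts the continuous titre first, and no text places sex, age within adults or other demographics in a titre model.

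The direction of the loss is certain and its size is not. Under the stated assumptions (two equal groups, second group lower, two-sided 5%, 70% to 95% seroconversion in the reference group) it is about 5 to 7 points at 0.2 SD with 102 participants. At 0.4 SD it is about 16 to 30 points with 102 and about 20 to 46 with 201. Since the analysis is a supporting one, the case for acting rests on the better method being nearly free, not on a threat to the trial's main conclusions.

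**What to change.** In section 7:
- Add, as the main demographic analysis, a linear or repeated-measures model of log10 ELISA titre on the demographic variables, with dose group and log10 baseline titre as covariates. Report geometric mean titre ratios with 95% confidence intervals.
- Keep the logistic model and Fisher's exact test for seroconversion as supporting analyses.
- Carry the synopsis' repeated-measures titre comparison between groups, with its allowance for baseline seropositivity, into section 7.

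The cost is wording and analysis code. Table 3 already schedules serology at screening and on days 7, 14, 28, 56, 84 and 180. One small downside is that titres below the detection limit need a stated substitution rule or a censored (Tobit) likelihood.
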